**SECTION D – PLAN FOR OBTAINING INFORMED CONSENT**

***Please complete the attached “Informed Consent Checklist” prior to completing this section.***

1. Describe how participants are to be recruited; if using advertisements include a sample with date.

Subjects will be recruited through advertisements around McMaster Campus, at local grocery stores and community centers and via a brief television appearance on the local Cable TV network in Hamilton (This was used successfully in an earlier training study in the elderly and more than twice the required subjects were recruited within a week).

1. Describe the relationship between the investigator(s) and the participant(s). Who will obtain consent?

Subjects will be not likely be known by any of the primary investigators. Informed consent will be obtained by either the study coordinator or one of the primary investigators.

1. Are participants competent to consent? [X ] YES [ ] NO If NO, describe the alternate source of consent.

If a minor, describe the procedure to be used. Where applicable, describe how you will obtain assent.

1. How will you assure ongoing consent from research participants?

The exercising participants will be required to come to the exercise training center twice a week (50 %). We will assume that their voluntary participation will indicate a willingness to continue in the study. There will be a mid-study (6 months) testing session where all aspects of the study will be reviewed. For the 50 % of participants who are not exercise training, they will come in for a 30 minute stretching session and to review any questions that arise.

1. What procedures will be followed for participants who wish to withdraw, either during or after the study?

Subjects who withdraw prior to randomization or within the first week (i.e., before the first testing session) will not be considered to have started the study and will be thanked for their interest. There are a few individuals who may use the study as a vehicle to obtain free exercise training and may drop out if they are not randomized to the exercise group. In our experience, this is about 5 – 10 % of all persons and we will notify people whether they are in the exercise groups or not before the first testing session. Once in the study (i.e., after the first testing session) all drop-outs will be considered in an intention to treat analysis of the data and the reason for the withdrawal will be noted and will be part of the final manuscript. Participants who experience any side effect from the study (i.e., tendonitis from exercise training) will be covered for the costs of treatment (such as physiotherapy or anti-inflammatories) and if they drop-out because of a negative consequence of the study, they will be given the full remuneration.

1. Will you be contacting participants either by telephone or letter during the project? [X] YES [ ] NO

If YES, append a copy of the telephone script or list of questions with the research protocol.

Participants will be contacted by telephone to book times for their testing sessions in order to fit into their schedule.

“Hello, this is ____________ calling from the older adult training study. We would like to plan the times for your testing sessions. We have a number of open testing sessions available including, ………… dates. If none of these times is convenient for you, are there times that would be more appropriate for you? Do you know how to get to the McMaster Medical Center, if not, we can send you a map or explain it over the phone. Thank you for participating in the study and we look forward to seeing you on (time and date).”

If participants miss more than one exercise session, they will be contacted to see if there is anything wrong (i.e., are they ill, injured, still interested in participating?).

“Hello, this is ____________ calling from the older adult training study. We noticed that you did not attend the exercise session on (date). I do hope that you and your family are healthy and hope to see you again soon. (if not home – “At your earliest convenience could you please give me a call at (number) if there are any questions.” Thank you again for participating in the study and we look forward to seeing you on (if they are home), or if they are not home …look forward to hearing from you.”

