***Research Plan.***

*1. Subjects.* N = 80 healthy males and females 65 - 85 y. *2. Design/Intervention.* Randomized, double-blind study with equal allocation to 4 treatment groups: 1. Resistance training (RT) (8 months, 3dwk-1) and placebo (PL) – Group = RT + PL; 2. RT as in # 1 + CrM (5 gd-1) and CLA (3 gd-1) supplementation– Group = RT+SUPP; 3. Sedentary (8 months of home stretching (SED)) and placebo (PL) = SED; 4. SED as in # 3 + SUPP as in # 2 – Group = SED+SUPP. *3. Major outcome variables.*A. Function – muscle strength (isometric and dynamic), aerobic capacity, functional tasks; B. Anthropometry – DEXA for fat-free mass, bone mineral content and density; C. Muscle – Histology – ATPase for fiber area and type, cytochrome oxidase (COX) negative fibers, COX sub-unit II and IV and 8-OH-2deoxyguanosine by IHC; Biochemistry – electron transport activity, creatine, ATP, phosphocreatine, protein carbonyls and anti-oxidant enzymes; Molecular biology – mitochondrial DNA deletions, gene expression pattern by micro-chip technology; D. Blood – CK activity, liver and renal function tests, bone turnover markers (osteocalcin and N-telopeptide); E. Urine - 8-OH-2deoxyguanosine/creatinine.

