  2. In our pilot study we had a drop-out rate of 7 %, and if we assume a drop-out rate of twice this (~ 6/group), we should retain 34 people at each of the two centers with 34 in RT and 34 on the combined supplement.

1. Design/Methodology:

Participants who are deemed eligible to participate will be randomly allocated into one of four groups. The allocation will be based upon an expected equal recruitment at the London (total = 40) and Hamilton (total = 40) sites and there will be 10 independent blocks of 4 randomly distributed interventions at each site (20 allocated to strength exercise (10 = + supplement; 10 = no supplement) and 20 allocated to no exercise (10 = + supplement; 10 = no supplement)) with an equal distribution:

1. Resistance training (RT) (12 months, 3dwk-1) and placebo (PL) – Group = RT + PL.

2. RT as in # 1 + CrM (5 gd-1) and CLA (3 gd-1) supplementation (SUPP) – Group = RT+SUPP.

3. Sedentary (12 months of home stretching (SED)) and placebo (PL) = SED.

4. SED as in # 3 + SUPP as in # 2 – Group = SED+SUPP.

1. Setting (e.g. outpatient, ICU, community):

The participants will be healthy ambulatory community dwelling men and women over the age of 65 y.

a. Exercise testing – Rm 4U18 and 2F MUMC (Neuromuscular research testing area – [name]).

b. Exercise training – Tue and Thur. – Ivor Wynne Center exercise center.

1. (a) Brief description of participants:

Men and women over the age of 65 y and less than 85 y who are living independently in the community with no contra-indications to exercise testing or training will be recruited.

(b) Are there any age, ethnicity, language, gender or race-related inclusion or exclusion criteria? [ ] YES [ X ] NO

If YES, please justify:

We plan to recruit equal numbers of men and women.

1. Study interventions:

a) Exercise training (50 % of recruits; other 50 % will continue with their usual routine) – participants will perform supervised strength/resistance exercise three times a week (Tue/Thur) for **12 months** using a machine based whole body exercise program that we have shown previously to be safe and effective (Brose, et al.,  *J Gerontol A Biol Sci Med Sci.*, 58:B11-9, 2003). Subjects will also perform a home based exercise routine on Saturday with rubber bands and resistance exercises not requiring weights (i.e., sit-ups).

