- Serum CK activity, bilirubin, gamma-glutamyl transferase (GGT), and creatinine will be taken pre-, at 6 months, and at the end of the study. The pre- and + 6 month values will be provided to two local staff physicians (gastroenterologist and cardiologist) who will review the data and determine if there are any alterations that require further investigation or withdrawl from the study.
- Exercise stress testing. Prior to starting the study, each participant will have a symptom limited exercise stress test completed to determine maximal oxygen consumption and to determine if there are any ECG abnormalities. Any abnormalities that are deemed to be a risk to participation in an exercise program will be used as an exclusion criteria and the family doctor will be provided with the test results for appropriate action. [name] will review the pre-study and + 6 month tests for study exclusion or study withdrawal at the 6 month testing period. A defibrillator will be on hand at the time of the testing and each subject will have a 12 lead ECG.
- General health risk. Each participant will complete a health questionnaire and will be screened by the research coordinator to ensure that there are no contra-indications to participation. The family doctor of each potential candidate will be contacted to determine whether there are any contra-indications to participation. Specific exclusion criteria will include: known coronary artery disease, congestive heart failure, renal failure, diabetes requiring insulin or > 5 mg Glyburide or equivalent, renal failure (creatinine > 120, potassium > 5.00 mmol/L), previous stroke, uncontrolled hypertension or hypertension requiring more than mono-pharmacotherapy, inability to consent due to cognitive difficulties, chronic obstructive pulmonary disease (FVC or FEV1 < 85 % of age predicted mean value or requiring any medication other than a puffer as needed) or joint related problem that would exclude them from performing the strength training. Furthermore, we shall exclude persons who have a hip or lumber spine bone mineral density that is > 2 SD below the age adjusted mean values (based upon the DEXA scan).

1. (a) Will participants be reimbursed for expenses? [X] YES [ ] NO

If YES, please provide amount(s) and item(s) covered.

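### Exercise allocation is disclosed before the first testing session and early leavers are not counted, so the analysis set is not intention to treat for exercise versus sedentary comparisons

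*Protocol*

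**What the plan says.** The rule is in the protocol, Section D, under procedures for participants who withdraw. It has four parts.

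- Who is not counted: "Subjects who withdraw prior to randomization or within the first week (i.e., before the first testing session) will not be considered to have started". Withdrawal before randomisation is listed separately, so the first-week clause also covers people already randomised.
- Why some will leave: a few people join for the free training and "may drop out if they are not randomized to the exercise group". The protocol puts this at about 5–10% of people.
- When they learn their arm: "we will notify people whether they are in the exercise groups or not before the first testing session".
- When counting starts: "Once in the study (i.e., after the first testing session) all drop-outs will be considered in an intention to treat analysis of the data". Reasons for withdrawal are promised for the manuscript only for this group.

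Three other places bear on the point. The Research Plan describes a "Randomized, double-blind study with equal allocation to 4 treatment groups". Section B, Part II, Design/Methodology says "Participants who are deemed eligible to participate will be randomly allocated into one of four groups". Section C, on managing risks, places the exercise stress test before the start of the study and says of its findings: "Any abnormalities that are deemed to be a risk to participation in an exercise program will be used as an exclusion criteria". It also excludes people on DEXA bone density.

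**The concern.** The order fixed in Section D is: randomise, disclose the exercise arm, let people leave, then test and begin to count. A person who leaves in that window leaves knowing the allocation, and the only motive the protocol names applies to those not allocated to exercise. Dropping these people is an exclusion after randomisation that depends on the arm. The set that remains cannot be called intention to treat for RT versus SED.

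Two things are at stake. First, the SED arms lose people who particularly wanted to exercise, while their counterparts in the RT arms have no such reason to go. The groups compared may then differ for reasons other than training. Nothing in the rule requires these early losses to be reported, and no testing-session baseline exists for them.

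Second, knee extension strength, machine strength and the functional tasks depend on effort. Under this order they are first measured in people who know whether they will train. Any difference in effort at baseline carries into the change from baseline. Its direction cannot be predicted from the documents.

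**Working it through.** **Inputs from the protocol.** Total 80, with 20 exercise and 20 sedentary at each of two sites, so 40 RT and 40 SED (Design/Methodology). Pilot drop-out 7%, doubled for planning, with 34 retained (Sample size). Refusal type about 5–10% (Section D).

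**The plan's own retention figure.** 2 × 7% = 14%. 40 × 0.14 = 5.6 lost and 40 × 0.86 = 34.4 retained, which agrees with the stated 6 and 34. The 14% is built from a pilot drop-out rate and does not mention refusals between disclosure and the first test.

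**How many are removed.** The 5–10% can be read in two ways.

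- A share of people who are of this type, of whom only those allocated to SED leave: 0.05 × 40 = 2 to 0.10 × 40 = 4. The comparison is 40 RT versus 36–38 SED.
- A share of all 80 who actually leave, all from SED: 0.05 × 80 = 4 to 0.10 × 80 = 8, or 10–20% of SED. The comparison is 40 RT versus 32–36 SED.

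The first is the more natural reading, because the percentage follows a description of a kind of recruit. If non-starters are not replaced (the protocol does not say), SED after 14% drop-out would be 38 × 0.86 = 32.7 to 36 × 0.86 = 31.0 on the first reading. On the second it would fall as low as 32 × 0.86 = 27.5.

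**Shift in the SED mean.** With a share g of SED removed, and those people differing from the remainder of the randomised SED population so that their mean is d SD away from the SED mean, the mean of those kept moves by g × d / (1 − g). The documents do not give d, so it is assumed over 0.25–1.0 SD. The last column is the two-sided type I error at nominal 0.05 for RT versus SED, by normal approximation, with shift / √(1/40 + 1/(40(1 − g))) as the displacement.

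| SED removed | g | d = 0.25 | d = 0.5 | d = 1.0 | Type I error, d = 0.25 / 0.5 / 1.0 |
|---|---|---|---|---|---|
| 2 of 40 | 0.05 | 0.013 | 0.026 | 0.053 | 0.050 / 0.052 / 0.056 |
| 4 of 40 | 0.10 | 0.028 | 0.056 | 0.111 | 0.052 / 0.057 / 0.077 |
| 8 of 40 | 0.20 | 0.0625 | 0.125 | 0.25 | 0.058 / 0.082 / 0.184 |

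For example, g = 0.10 and d = 0.5 gives 0.10 × 0.5 / 0.90 = 0.056 SD. These figures cover selection only. The documents give nothing from which to size an effect of disclosure on baseline effort.

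**The case against.** The strongest case against is that the damage is limited.

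- **Supplement contrasts.** The main research question concerns the supplements, and the worked sample sizes compare supplement with placebo. Only exercise status is disclosed, and the motive to leave does not depend on the supplement arm. This stands: those contrasts are largely spared.
- **Size.** On the more natural reading 2–4 people are removed, and the shift at d = 0.5 is only 0.026–0.056 SD. This stands. Power is not the problem either, since the protocol puts most exercise versus sedentary comparisons at fewer than 10 per group.
- **RT arms.** A reader might infer that the RT arms keep everyone. The first-week rule applies to all arms, and the protocol says only that some people have a reason to leave if not given exercise. The imbalance is a well-supported inference, not a stated fact.
- **Eligibility and VO2max.** A reader might infer that testing after allocation contradicts the use of the stress test and DEXA for eligibility, or that baseline VO2max is measured in people who know their arm. Neither is shown. Screening stress test and DEXA, then randomisation, then the first testing session is a consistent order. The protocol does not define that session against the screening tests.
- **Blinding.** Supervised training cannot be masked, and placebo is nested within each exercise condition. The double-blind label needs a clarifying phrase and is not itself a source of bias.
- **Remedy.** Moving the tests does not produce 6- or 12-month outcomes for refusers. This stands, and the fix has to allow for it.

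What the objection does not remove is the rule itself. Section D excludes randomised people who know their arm and then uses the intention-to-treat label for those who remain.

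**Conclusion.** The point holds for RT versus SED. As written, the analysis set omits randomised participants for a reason tied to their allocation, probably 2–4 of 40 SED and at most 8 on the wider reading. Strength and functional baselines follow disclosure of the exercise arm.

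The bias from selection is likely to be small: about 0.03–0.06 SD at 2–4 removed and 0.13 SD at 8 removed, if refusers differ by 0.5 SD. It becomes material only with high refusal and a large difference (0.25 SD and type I error of about 0.18 at 8 removed and 1.0 SD). These figures assume that refusals occur only in SED, and the difference between refusers and others is an assumption with no source in the documents.

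The documents do not support extending the point to supplement versus placebo, to baseline VO2max or DEXA, or to a contradiction in eligibility. It should be fixed, because exclusions made this way leave no data from which to correct the comparison later, but it does not undermine the trial as a whole.

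**What to change.** 1. Complete the baseline strength and functional tests, together with the screening stress test and DEXA, before randomisation and before anyone is told the exercise arm. Define the first testing session accordingly.
2. Define the intention-to-treat set as everyone randomised. Remove the first-week exclusion for randomised people; it can remain for those who withdraw before randomisation.
3. Report early refusals by arm with reasons, seek their 6- and 12-month outcomes, and treat those not obtained as missing data.
4. State that double-blind applies to the supplement factor only.

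The cost is a change in visit order and about 2–8 baseline sessions on people who then decline. Some follow-up will still be missing for refusers, but the loss will be visible by arm, with a baseline for each person, instead of being hidden by the definition of the set.

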**SECTION E – STEPS TO BE TAKEN TO ENSURE CONFIDENTIALITY OF DATA**

1. How will identity of participant(s) be protected?

The names of the participants will be used only on the original documents for identification, remunerations cheque mailing, and to send a copy of the final paper and a lay summary with their own personal data. The publications will not contain any identifiers that could possibly be used to identify the person’s identity.

1. Where and how will the data be stored; and who will supervise access to the data to ensure confidentiality is maintained?

[name] will ultimately supervise access to the data in Hamilton and [name] in London. The research coordinator (McMaster site) will organize and centralize the data and will store a “mega copy” of all the data at McMaster in his or her office (4U20) – locked office and filing cabinet.
